#### Harm

Apart from the risk of data violations, there is no anticipated harm to the study participants. The investigator will be identified by experimenter number to reduce the risk. Although greater adherence to treatment is expected in the intervention group, no systematic differences in diabetes management are expected.

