**Elimination criteria**
Patients whose condition worsens, resulting in a hospitalization duration exceeding 14 days and increased hospitalization costs.Patients with concomitant systemic diseases that require special treatment, leading to a hospitalization duration exceeding 14 days and increased costs.Patients with serious complications that arise during the course of treatment and necessitate discontinuation of the nursing pathway.Patient and family preferences and wishes that affect the implementation of this nursing pathway.

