### Interventions

#### Intervention Plan

Upon admission, nurses provide admission education and assign eligible patients to the study group or the control group based on the time of admission (Figure 1). The intervention plans for both groups are outlined in a pathway form and include 3 components: executing medical orders, nursing tasks, and health education, along with TCM-specific treatments (Multimedia Appendix 1). For the control group, nurses subjectively implement the nursing plan according to the pathway form. The study group strictly follows the TCM nursing pathway for T2DM.

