#### Implementation of the TCM Nursing Pathway for T2DM

Upon admission, nurses provide admission education and assess the patient’s condition using an evaluation form for the TCM nursing pathway for T2DM. This assessment determines whether the patient qualifies for inclusion in the study. Eligible patients receive the TCM nursing pathway for T2DM. For patients included in the study, nurses ensure that physicians perform a thorough examination upon admission. The TCM nursing pathway form for T2DM is distributed, and patients are informed about their treatment and the nursing plan during hospitalization. This ensures patients understand the medical and nursing measures to be implemented.

During hospitalization, the responsible nurse uses the evaluation form of the TCM nursing pathway for T2DM to develop an appropriate care plan. This plan may include TCM techniques, syndrome differentiation–based dietary therapy, exercise and health practices, herbal prescriptions, and emotional regulation. The study group strictly adheres to the schedule outlined in the TCM nursing pathway for T2DM. Nurses coordinate with relevant departments promptly to complete necessary examinations. The control group receives routine care.

If there are any changes in the patient’s condition, the responsible nurse promptly analyzes and addresses the changes, adjusting the sequence of items in the TCM nursing pathway as necessary. The head nurse checks the implementation of the TCM nursing pathway for T2DM and the routine care plan daily. The head nurse ensures compliance with the nursing pathway protocol and evaluates the quality of care promptly. Relevant data are collected and evaluated at the time of the patient’s discharge.

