### Ethical Considerations

The ethical principles guiding this study include the Measures for Ethical Review of Biomedical Research Involving Humans, Good Clinical Practice for Drug Trials, Regulations on Clinical Trials of Medical Devices, Ethical Review Guidance for Drug Clinical Trials, Clinical Ethical Review Management Guidelines for Traditional Chinese Medicine Hospitals, the Declaration of Helsinki, and the International Ethical Guidelines for Biomedical Research Involving Human Subjects.

The trial has been approved by the Ethics Committee of Guang’anmen Hospital, China Academy of Chinese Medical Sciences (2022-022-KY-01). Prior to the implementation of the study, informed consent must be obtained from patients. Participation in this study is entirely voluntary. Patients may choose not to participate or withdraw from the study at any time without providing a reason, and participation requires signing an informed consent form.

All patient data collected during the trial will remain confidential. Medical records will be identified using research ID numbers instead of names. Identifiable information will not be disclosed to anyone outside the research team unless the patient provides explicit permission.

In accordance with relevant national regulations, in the event of research-related injuries, the study institution, Guang’anmen Hospital of the China Academy of Chinese Medical Sciences, will bear the corresponding medical costs and provide appropriate financial compensation.

For any questions regarding participant rights in this study, individuals can contact the Ethics Committee of Guang’anmen Hospital, China Academy of Chinese Medical Sciences.

The study form will be kept by the data collector in a folder in the study office. Study data will be processed without participants being recognizable. Only the researcher responsible for the analysis can access the final data set; after the trial study is published, we will provide research references and the scientific basis for relevant clinical practice, formulate the implementation specifications of the nursing program under the chosen pathway, and promote the research results in the industry.

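### The article anticipates no harm beyond data risk, yet it allows herbal prescriptions and TCM techniques and eliminates patients with serious complications or costly worsening, so signs of harm could drop out of the comparison between arms

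*Protocol article*

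**What the plan says.** In the Protocol article, the Harm section takes a position: "Apart from the risk of data violations, there is no anticipated harm to the study participants". It expects better treatment adherence in the intervention group, but adds that "no systematic differences in diabetes management are expected".

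On content, the section on implementing the pathway says: "This plan may include TCM techniques, syndrome differentiation–based dietary therapy, exercise and health practices, herbal prescriptions, and emotional regulation". The Intervention Plan section describes a pathway form for both groups, covering "executing medical orders, nursing tasks, and health education, along with TCM-specific treatments". The study group follows its pathway strictly, while nurses apply the control group's plan at their own judgment.

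Two of the elimination criteria in Textbox 1 matter here:

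- "Patients with serious complications that arise during the course of treatment and necessitate discontinuation of the nursing pathway"
- "Patients whose condition worsens, resulting in a hospitalization duration exceeding 14 days and increased hospitalization costs"

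The Outcomes section lists quality of life as primary. The secondary indicators are length of stay, costs, glucose control, symptom scores, satisfaction and health knowledge. Data are collected one day before discharge and 4, 12 and 24 weeks after it. The Ethical Considerations section provides for costs and compensation "in the event of research-related injuries".

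**The concern.** An article that merely left adverse-event procedures to its full protocol would raise no issue. This one goes further. It says that no harm is expected, and it fixes a rule under which patients who do badly are eliminated.

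The statement is hard to square with an intervention that may involve ingested and physical treatments in inpatients with diabetes, and with a criterion written for serious complications during treatment. The elimination rule also acts after allocation and depends on how the patient fares. If elimination means leaving the comparison, the patients most likely to show harm are the ones removed. The Future Directions section plans to promote the pathway in more hospitals, and that step would then rest on evidence with no stated comparative safety component.

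**Working it through.** The plan gives no figure on this point, so the check is mainly a comparison of sections.

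**Step 1: expected harm against intervention content.** The Harm section limits anticipated harm to data risk. The implementation section allows herbal prescriptions and TCM techniques. No sentence explains why these carry no anticipated risk, so the two sections need reconciling.

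**Step 2: when elimination acts.** Patients are assigned on admission (Intervention Plan). The two criteria quoted above describe events during treatment or a stay that has passed 14 days. Both can only be met after assignment, so elimination depends on a post-randomization outcome.

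**Step 3: which signs of harm remain.**

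| Possible sign of harm | Listed as an outcome? | Affected by elimination? |
|---|---|---|
| Serious complication | No | Yes, if it ends the pathway |
| Long stay | Yes (length of stay) | Yes, if due to worsening, over 14 days and with higher costs |
| High cost | Yes (medical costs) | Yes, under the same criterion |
| Poor glucose control or symptoms | Yes | Yes for eliminated patients, if elimination ends their follow-up |

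The direct sign has no listed outcome. The indirect signs are cut off in the patients in whom they would be most marked.

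**Step 4: how many patients this might concern.** The inputs are 297 per arm (Sample Size Calculation) and a serious-complication rate p. The documents give no p, so the values below are assumptions with no anchor in the article. Expected cases per arm are 297 × p. The chance of at least one case in an arm is 1 − (1 − p)^297.

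| Assumed p | Expected cases per arm | Chance of at least one |
|---|---|---|
| 0.5% | 297 × 0.005 = 1.5 | 77% |
| 1% | 297 × 0.01 = 3.0 | 95% |
| 2% | 297 × 0.02 = 5.9 | 99.8% |
| 5% | 297 × 0.05 = 14.9 | nearly 100% |

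Even at low rates the criterion would probably be used, though for few patients.

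**Step 5: what a safety table could show.** With 297 per arm, the power to detect a doubling of the rate is about 17% for 1% against 2%, 30% for 2% against 4%, and 64% for 5% against 10%. A table by arm would therefore be descriptive. With no events in 297 patients, the rule of three gives an upper 95% limit of about 3/297 = 1.0%.

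**The case against.** The other side has several good points.

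- **Cause.** The Harm section can be read as being about harm from taking part. The elimination criterion does not attribute complications to the intervention, and inpatients with type 2 diabetes can deteriorate from their disease. Expecting no harm from a nursing pathway while foreseeing some deterioration is not a strict contradiction. This stands. A reader might infer that the article admits to harm from the pathway, and it does not. But a comparison by arm is how disease and intervention would be told apart, and elimination weakens that comparison.
- **Exposure.** A reader might infer that herbal and TCM items are a new risk in the study group only. The article does not support this. Both groups' forms carry TCM-specific treatments, and the implementation section says only that the plan may include herbal prescriptions. The added exposure is unproven.
- **Symmetry.** A reader might infer that only study patients can be eliminated for stopping the pathway. The criterion names no arm, and both groups have a pathway form, although controls are elsewhere said to receive routine care. The wording leaves this open. Even symmetrical criteria would condition the comparison on an outcome.
- **Silence.** Adverse-event forms and safety tables may sit in the full protocol. The article also does not say whether eliminated patients are followed or reported, and it has nurses respond to changes in condition. This stands, and it is why harm could go unseen, not why it would.
- **Compensation.** The injury clause is tied to national regulations. It is a contingency and carries little weight as a forecast of harm.

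**Conclusion.** The point holds in a limited form. The no-harm sentence fits poorly with the described content of care and with the elimination criteria. Together with an outcome list that has no safety item, those criteria could take both the direct and the indirect signs of harm out of the comparison between arms. This follows from a stated position and a stated rule, not from silence alone.

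The conclusion assumes that eliminated patients leave the comparison, which is the ordinary meaning of the term but is not spelled out. Its size cannot be derived from the article. The assumed rates suggest from one or two to about 15 patients per arm.

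A reader might go further and conclude that harm will be hidden, or that the pathway is unsafe. The article supports neither. The change is worth making because it is cheap and removes a dependence on outcome that serves no stated analytical purpose.

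**What to change.** 1. Reconcile the Harm section, the implementation section and the elimination criteria, and replace the sentence that anticipates no harm with one that fits the described interventions. Which events should end the pathway is a clinical matter and is not addressed here.
2. State that stopping the pathway, or meeting an elimination criterion, does not remove a patient from follow-up or reporting.
3. Tabulate serious complications and adverse events by arm for all randomized patients, with eliminated patients included and marked. Present the table as descriptive.
4. Record these events prospectively at the existing visits (before discharge and weeks 4, 12 and 24). For patients already enrolled, take them from hospital records.

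The cost is slightly more recording by ward staff and one extra table. The 202 patients already randomized, 202/594 = 34% of the planned total, need some retrospective chart work, and their records may be less complete. The other 594 − 202 = 392 could be covered prospectively, counting from the article's status report. If the full protocol already contains these provisions, the change reduces to correcting the article's wording.

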### Ethical Considerations

The ethical principles guiding this study include the Measures for Ethical Review of Biomedical Research Involving Humans, Good Clinical Practice for Drug Trials, Regulations on Clinical Trials of Medical Devices, Ethical Review Guidance for Drug Clinical Trials, Clinical Ethical Review Management Guidelines for Traditional Chinese Medicine Hospitals, the Declaration of Helsinki, and the International Ethical Guidelines for Biomedical Research Involving Human Subjects.

The trial has been approved by the Ethics Committee of Guang’anmen Hospital, China Academy of Chinese Medical Sciences (2022-022-KY-01). Prior to the implementation of the study, informed consent must be obtained from patients. Participation in this study is entirely voluntary. Patients may choose not to participate or withdraw from the study at any time without providing a reason, and participation requires signing an informed consent form.

All patient data collected during the trial will remain confidential. Medical records will be identified using research ID numbers instead of names. Identifiable information will not be disclosed to anyone outside the research team unless the patient provides explicit permission.

In accordance with relevant national regulations, in the event of research-related injuries, the study institution, Guang’anmen Hospital of the China Academy of Chinese Medical Sciences, will bear the corresponding medical costs and provide appropriate financial compensation.

For any questions regarding participant rights in this study, individuals can contact the Ethics Committee of Guang’anmen Hospital, China Academy of Chinese Medical Sciences.

The study form will be kept by the data collector in a folder in the study office. Study data will be processed without participants being recognizable. Only the researcher responsible for the analysis can access the final data set; after the trial study is published, we will provide research references and the scientific basis for relevant clinical practice, formulate the implementation specifications of the nursing program under the chosen pathway, and promote the research results in the industry.

### Statistical Analysis

We will use SPSS (version 26.0; IBM Corp) to perform the statistical analysis. Descriptive statistics for quantitative variables will include at least the mean and SD or the median and IQR. Descriptive statistics for qualitative variables will include at least the frequency and percentage for each category. Comparisons between the 2 groups will be conducted using an independent-sample *t* test (for normally distributed data with equal variances) or the nonparametric rank-sum test. For unordered categorical data, comparisons between the 2 groups will be made using the *χ*^2^ test or Fisher exact test, while ordinal categorical data will be analyzed using nonparametric tests. All statistical tests will be 2-sided, with a *P*<.05 considered statistically significant.

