**Methods:**

This study uses a prospective, randomized, single-blind, parallel-controlled design. Based on sample size calculations, the study will include 594 patients with diabetes, with 2 groups of 297 patients: an observation group will receive a TCM nursing program based on clinical pathways, while a control group will receive routine care. Both groups will be evaluated before and after the intervention using assessment indicators. The primary outcome is the quality of life score, measured by a diabetes-specific quality of life questionnaire. Secondary outcomes include hospital stay duration, medical expenses, health knowledge, blood glucose control, symptom scores, and patient satisfaction.

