#### Sample Size Calculation

A literature-based approach was used to compare the preset effect, with α=.05 and β=.10, against the known efficacy of general nursing from previous studies. Based on methods found in the literature [10] and conclusions from earlier research, the historical effective rate (very satisfied + satisfied) was determined to be approximately 74.5% [9]. The effective rate for this pathway nursing program is projected to be 85%. Using *Z* values from standard tables (*Z*1 – α / 2 = 1.96; *Z*1 – β = 1.28), the sample size for each group was estimated as follows:

N1 = N2 = (*Z*1 – α / 2 + *Z*1 – β) 2 [P1(1 – P1) + P2(1 – P2)] / δ2 = (1.96 + 1.28) 2 [0.745 × (1 – 0.745) + 0.85 × (1 – 0.85)] / (0.85 – 0.745) 2 = 296. Thus, 242,272 indicated 297 cases, and the sample size of this study was 297 × 2 = 594 cases.

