#### Outcomes

Researchers use standardized questionnaires to collect baseline data. The primary efficacy indicator is a quality of life scale (the Diabetes-Specific Quality of Life Scale) [11]. Secondary efficacy indicators include the length of hospital stay, medical costs, blood glucose control, patient symptom scores, patient satisfaction, and the level of health knowledge acquired at admission. Data are collected 1 day before discharge and at 4 weeks, 12 weeks, and 24 weeks after discharge.

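### The stated t test or rank-sum rule leaves the baseline quality-of-life score unused as a covariate and sends unequal variances to a test that does not compare means

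*Protocol article*

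**What the plan says.** The Statistical Analysis section of the protocol article gives one rule for comparing quantitative outcomes between groups. It is an independent-sample t test, with the condition and the alternative worded as "for normally distributed data with equal variances) or the nonparametric rank-sum test". It names no covariate and no repeated-measures model, and it has no separate method for costs or length of stay. It adds that "All statistical tests will be 2-sided".

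The same article shows that baseline data exist. The Abstract (Methods) states that "Both groups will be evaluated before and after the intervention using assessment indicators". The Outcomes section states that "Researchers use standardized questionnaires to collect baseline data", then lists four later collection times: the day before discharge, and 4, 12 and 24 weeks after it. The primary outcome is the diabetes-specific quality-of-life score. Length of stay, medical costs, blood glucose control and symptom scores are among the secondary outcomes.

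**The concern.** Two features of the rule are weak as written.

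First, a score measured at admission usually predicts the same score later. A plain two-sample test on the later score leaves that predictable part in the error term. The trial pays to collect the baseline and then gains no precision from it on its primary outcome.

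Second, the rule makes equal variance a condition for comparing means. If the spreads differ, the analysis moves to the rank-sum test, so the quantity being tested depends on a feature of the data. The rank-sum test is no remedy for unequal spread, because its null hypothesis is that the two distributions are identical. It also yields no mean difference. This matters most for medical costs, where a reader will want to know how much was saved per patient.

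**Working it through.** **The plan's own figure.** Inputs from Sample Size Calculation: "with α=.05 and β=.10"; control, "the historical effective rate (very satisfied + satisfied) was determined to be approximately 74.5" percent; intervention, "The effective rate for this pathway nursing program is projected to be 85" percent; and "the sample size of this study was 297 × 2 = 594 cases". The printed formula gives

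(1.96 + 1.28)² × [0.745 × 0.255 + 0.85 × 0.15] / 0.105² = 10.4976 × 0.317475 / 0.011025 = 302.29, so 303 per group.

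The article prints 296 and uses 297, which is 6 patients (2.0%) below 303. That discrepancy is a separate matter. What matters here is that the size was set on a satisfaction proportion, so it does not depend on how quality of life is analysed. I take 297 per group as given.

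**Precision on a quantitative score.** The smallest standardized difference detectable with 90% power, two-sided 5%, is

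d = (1.960 + 1.2816) × √(2 × V / 297),

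where V is the variance relative to a t test on the follow-up score. V = 1 for that t test, V = 1 − r² for ANCOVA on baseline, and V = 2(1 − r) for a t test on change (assuming equal variance at baseline and follow-up). The article gives no correlation r, so 0.3 to 0.7 is an assumed range. With V = 1, d = 3.2416 × √(2/297) = 0.266 SD.

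| r (assumed) | V, ANCOVA | Variance cut | d, ANCOVA | Equivalent n per group, unadjusted | V, change score |
|---|---|---|---|---|---|
| 0.3 | 0.91 | 9% | 0.254 | 326 | 1.4 |
| 0.5 | 0.75 | 25% | 0.230 | 396 | 1.0 |
| 0.7 | 0.51 | 49% | 0.190 | 582 | 0.6 |

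An effect with 80% power under the unadjusted test would have 83.6%, 89.9% or 97.5% under ANCOVA. Against a change score, the ANCOVA variance ratio is (1 − r²) / [2(1 − r)] = (1 + r)/2, that is 0.65, 0.75 or 0.85. ANCOVA is therefore ahead whichever score the t test was meant for.

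**The equal-variance condition.** With equal group sizes n, the pooled squared standard error is [(s₁² + s₂²)/2] × (2/n) = (s₁² + s₂²)/n, which is the Welch value. Under 1:1 allocation the condition protects against almost nothing, and Welch's test covers any imbalance left by dropout.

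**Costs.** The following uses lognormal costs with 297 per group. The log-SDs are illustrations; the article gives no cost distribution.

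- *Equal means.* At log-SD 0.6 in both arms the rank-sum test rejects in about 5% of trials. At 0.6 vs 0.5 it rejects in about 22%, and at 0.6 vs 0.4 in about 64%, where Welch's test stays near 5%. In that last case the medians differ by a factor of exp[(0.36 − 0.16)/2] = exp(0.10) = 1.105.
- *Equal medians.* At log-SD 0.5 vs 0.7 the ratio of means is exp[(0.25 − 0.49)/2] = 0.89. The rank-sum test rejects in 5.0% and Welch in 55.7%. At 0.4 vs 0.8 the ratio is 0.79, with 5.9% against 98.0%.

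When spreads differ, the two tests can disagree in either direction. When spreads are equal, they do not conflict in this way.

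**The case against.** - **Unadjusted does not mean wrong.** A reader might infer that the primary analysis is biased or invalid. It is not. Under randomization a two-sample test holds its error rate, and chance baseline imbalance is already allowed for in it. The gain from adjustment also depends on an unknown correlation and is small at r = 0.3. No stated power is lost, because the sample size was not built on quality of life. All of this stands.
- **Baseline may not be ignored altogether.** The article does not say whether the t test is applied to follow-up scores or to change, and a change score does use baseline. This stands, so the supportable statement is that baseline is not used as a covariate.
- **The wrong question for costs and stay.** A reader might go further and say that the rank-sum test answers the wrong question for both. No section sets a mean difference as the target, and medians are allowed as descriptive statistics. For length of stay a rank or median comparison is a reasonable choice. Nor does the article show that costs are skewed enough to reach the rank-sum branch; its elimination criteria for stays beyond 14 days with increased costs could shorten the upper tail. The 64% figure is not a false-positive rate in general. It belongs to one assumed scenario in which the distributions, and their medians, really do differ.
- **This is detail for the statistical analysis plan.** That would be a full answer if the article were silent. It is not: it states the tests and the condition for switching between them. The objection fails for that rule, although it is fair for finer modelling detail.

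**Conclusion.** The point holds as a matter of efficiency and of a poorly chosen switching rule, and no further. Relative to a t test on follow-up scores, baseline adjustment would cut variance by 9%, 25% or 49% at assumed r = 0.3, 0.5 or 0.7. That lowers the 90% detectable difference from 0.266 SD to 0.254, 0.230 or 0.190 SD with all 297 per group analysed. The comparison with change scores rests on equal variances at the two times.

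Moving to the rank-sum test because variances differ is unhelpful whatever the correlation. For costs, the supportable conclusion is limited: a rank-sum test does not estimate a saving, and it can disagree with the mean difference when spreads differ. Whether they will differ in this trial is unknown.

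**What to change.** 1. For quality of life, and for other quantitative outcomes with an admission value (for example glucose and symptom scores), replace the rule with ANCOVA on baseline at each analysed visit, or a repeated-measures mixed model that includes baseline. Report the adjusted mean difference with a 95% confidence interval. The article names no primary visit, so the wording should not presuppose one.
2. Where an outcome has no baseline, use Welch's t test and delete the equal-variance condition.
3. For medical costs, also report the mean difference with a Welch or bootstrap 95% confidence interval. A rank-sum test may sit beside it.
4. A rank-based comparison may remain for length of stay.

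The cost is wording only. SPSS 26 can fit these analyses and no new data are needed. The Abstract (Results) reports that no statistical analysis had been done, so on that account the change can be fixed in advance without knowledge of the results.
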